### Randomization and allocation

This clinical trial is a multicenter, randomized, parallel-controlled design. Randomization and sectionalization of subjects will occur centrally using a CRMS and patients will be randomly generated codes according to the treatment group or the control group in a 1:1 ratio. Potential participants will be identified via databases of four hospitals and then interviewed by phone for interest and eligibility.

When the participants meet the inclusion or exclusion criteria and have signed the Informed Consent Form, researchers will access the CRMS and then input stratification factor according to the system’s prompt. The CRMS will display a participant identification code and a random number. The participant identification code or the random number is the only form of patient identity that distinguishes the treatment group from the control group. The flow of participants in the study, including the numbers analyzed for short-term and 6-month follow-up, are shown in Fig. 1.

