## Methods/design

### Study design

This clinical trial is a multicenter, parallel-group, randomized controlled design. Subjects will be enrolled at four hospitals: (1) The affiliated Hospital of Shaanxi University of TCM; (2) Shaanxi Provincial Hospital of TCM; (3) Xi’an Municipal Hospital of TCM; and (4) The Red Cross hospital of Xi’an.

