### Statistical analysis

The data will be collected and analyzed according to the intention-to-treat principle. Standard statistical techniques will be used to describe patients’ characteristics in both groups. We will compare baseline characteristics in both groups and, if incomparability appears, we will perform the secondary analysis, adjusting for differences. The primary outcome, VAS, will be compared between both groups using analysis of variance for repeated measures. If adjustment for possible baseline incomparability is needed, analysis of covariance will be done.

All data were analyzed statistically using SAS 9.2 version statistical software. Measurement data were expressed as mean ± standard deviation $$ \left(\tilde{x}\pm s\right) $$, and analyzed using a *t* test; rates were compared using the chi-square test. *P* < 0.05 will be used to indicated that the difference was statistically significant.

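### Randomisation is stratified by an unnamed factor, but the stated analyses leave that factor out and allow adjustment only when baseline imbalance is seen

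*Protocol article*

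**What the plan says.** **Design.** The Study design section states: "This clinical trial is a multicenter, parallel-group, randomized controlled design", and "Subjects will be enrolled at four hospitals". Under Randomization and allocation, patients are assigned to "the treatment group or the control group in a 1:1 ratio" through a central system, and "researchers will access the CRMS and then input stratification factor". The article names neither the factor nor its levels. It does not say that hospital is the factor, and it describes no blocking or minimisation.

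**Analysis.** The Statistical analysis section says: "The primary outcome, VAS, will be compared between both groups using analysis of variance for repeated measures". On covariates it says: "If adjustment for possible baseline incomparability is needed, analysis of covariance will be done". A preceding sentence likewise makes an adjusted secondary analysis depend on baseline differences being found. Other measurement data are "analyzed using a *t* test; rates were compared using the chi-square test". No stated analysis carries the stratification factor or hospital.

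**The concern.** Stratified allocation with balance inside strata removes between-stratum variation from the treatment contrast. An analysis that ignores the strata leaves that variation in its error term. The reported standard error is then larger than the true one, the test rejects too rarely under the null, and the precision that stratification could provide goes unused.

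The article does more than stay silent on model terms. It gives a rule for when to adjust, and that rule works against the stratification factor. Adjustment is triggered by observed baseline differences, whereas stratifying is meant to keep the groups alike on this factor. A detailed analysis plan that followed the rule would tend to leave out the one covariate that the design calls for. It would also let the form of the primary model depend on the data.

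**Working it through.** **Inputs from the article (Sample size considerations).** About 98 per group, alpha 0.05 one-sided, beta 0.1, 20% loss, 240 in total. The formula is n = 2[(tα + tβ)s/δ]². No numbers are given for s or δ.

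**The plan's own figure.** The 98 cannot be reproduced without s and δ, so the standardised effect was solved back from it:

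δ/s = (1.645 + 1.282) × √(2/98) = 2.926/7 = 0.418.

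For the total, 98/(1 − 0.2) gives 123 per group (246), and 98 × 1.2 gives 118 per group (236). The stated 240 lies between them.

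**Assumed input.** R is the share of VAS variance explained by the stratification factor. The article gives no figure, so a range of 0 to 0.20 is used. Balance within strata is also assumed, and s is taken as the total SD.

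**Formulas, for a between-group comparison of means**

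- True variance of the difference: (1 − R) × 2s²/n. The unadjusted test uses 2s²/n.
- Ratio of estimated to true SE: 1/√(1 − R).
- Actual one-sided type I error, unadjusted: 1 − Φ(1.645/√(1 − R)).
- Power, unadjusted: Φ((2.926 − 1.645)/√(1 − R)).
- Power with the factor in the model: Φ(2.926/√(1 − R) − 1.645).

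For example, at R = 0.10, 1/√0.90 = 1.054. Type I error is 1 − Φ(1.734) = 0.042. Unadjusted power is Φ(1.351) = 91.2%, and adjusted power is Φ(1.440) = 92.5%.

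| R | SE too large by | Actual one-sided type I error | Power, unadjusted | Power, adjusted | Gain (points) |
|---|---|---|---|---|---|
| 0 | 0% | 0.050 | 90.0% | 90.0% | 0 |
| 0.05 | 2.6% | 0.046 | 90.6% | 91.3% | 0.7 |
| 0.10 | 5.4% | 0.042 | 91.2% | 92.5% | 1.3 |
| 0.20 | 11.8% | 0.033 | 92.4% | 94.8% | 2.4 |

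**Check by simulation** (four strata, 98 per group, 20,000 runs, t tests). At R = 0.10, type I error was 0.040 unadjusted and 0.048 adjusted, and power was 90.9% and 92.3%. At R = 0.20, type I error was 0.035 and 0.051, and power was 91.8% and 94.4%. At R = 0 the two analyses agreed (power 89.6% and 89.7%; the normal approximation gives 90.0%).

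**The case against.** The strongest reply is that a journal article condenses the full plan and that model terms such as stratum or centre are usually left to the statistical analysis plan, which is not at hand. That disposes of the bare omission. It does not dispose of the stated adjustment rule, which ties adjustment to observed imbalance and so points away from the stratification factor.

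Other replies stand and limit the point:

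- **The loss is conditional.** If the factor does not predict VAS, nothing is lost. The argument also needs balance within strata, which the article implies by stratifying but does not describe.
- **Hospital is not shown to be the factor.** A reader might infer it from the four sites, but the article mentions hospitals only as places of recruitment and treatment. Adding hospital when it is not the factor is sensible modelling, not a consequence of the stated stratification.
- **The figures fit one kind of comparison.** They apply to the group main effect or to a single visit. A group-by-time interaction is tested against within-patient error, where stable differences between strata cancel.
- **Rates.** No efficacy outcome is defined as a rate, so no case is made here for changing the chi-square tests.

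A reader might also infer that the trial is already short of its stated power and that ignoring the strata makes this worse. That reading applies a two-sided 5% test to the 0.418 SD solved from the one-sided design. The sample size section specifies a one-sided test, and the analysis section gives a P threshold without sidedness. On the stated one-sided basis, unadjusted power at 98 per group is 90.0% to 92.4% over the assumed range.

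**Conclusion.** The point holds as a mismatch between design and analysis with a modest, conservative effect. Randomisation uses a factor that the stated analyses omit, and the stated condition for adjustment would normally not be met for that factor. For a factor explaining 5% to 20% of VAS variance, standard errors in an unadjusted between-group comparison would be 2.6% to 11.8% too large, one-sided type I error would be 0.046 to 0.033 instead of 0.050, and 0.7 to 2.4 points of power would be forgone relative to an adjusted analysis. At 0% nothing is lost.

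This rests on an assumed variance share, balance within strata, 98 analysed per group and the effect implied by the sample size. The treatment estimate is not biased, false positives do not increase, and power planned on the one-sided basis is not eroded. The change is worth making because it costs almost nothing.

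**What to change.** In the Statistical analysis section, name the factor used in the central randomisation system and its levels. State that it enters the primary VAS model as a fixed effect, together with hospital if hospital is a different variable. Do the same in the models for the continuous secondary outcomes (Borden measurement, NDI, SF-36). Say that these terms are included regardless of observed baseline imbalance, so that the data-dependent trigger no longer governs them.

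The change is one of wording. It uses a few degrees of freedom: 4 − 1 = 3 if the factor is the four hospitals, against 2 × 98 = 196 analysed patients. Sample size, visits and data collection stay as they are.

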**Fig. 1 Fig1:**
[figure not shown]
Flow diagram of recruitment process, group allocation and participation in the two interventions. All participants who completed a follow-up were included in the corresponding analysis

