### Outcome measurements

The primary outcome is pain severity measured with a Visual Analog Scale (VAS) at baseline, 20 days of the treatment duration and 1- and 3-month follow-up. Secondary outcomes include cervical curvature measured using the Borden method, a composite of functional status measured by the Neck Disability Index (NDI), patient health status (evaluated by the SF-36 health survey) and adverse events (AEs) as reported in the trial.

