### Sample size considerations

We calculated the sample size for this two-arm trial on the basis of comparing BCT versus TT, using the superiority test formula:$$ {n}_1={n}_2=2{\left[\left(ta+t\beta \right)s/\delta \right]}^2, $$where *tα* and *tβ* are constants, *s* is the estimated standard difference and *δ* is the mean value of the VAS for neck pain. The patients’ numbers were arranged in equal proportion and a superiority one-sided test was employed. Setting alpha at 0.05 and beta at 0.1, the calculated sample size of each group is around 98. Considering 20 % loss to follow-up, the total sample size needed to detect this difference at a 5 % level of significance with a power of 90 % is 240 patients [15, 16].

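### The article promises intention-to-treat, but the Fig. 1 caption ties each analysis to completing that follow-up, and the named repeated-measures ANOVA may narrow the set further

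*Protocol article*

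**What the plan says.** The article makes two statements about who is analysed.

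- Statistical analysis: "The data will be collected and analyzed according to the intention-to-treat principle".
- Fig. 1 caption: "All participants who completed a follow-up were included in the corresponding analysis".

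The Randomization and allocation section points to the figure for the participant flow, "including the numbers analyzed for short-term and 6-month follow-up, are shown in Fig. 1", so the caption belongs to the display that gives the analysis denominators.

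Three other statements bear on the point.

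- Method (Statistical analysis): "The primary outcome, VAS, will be compared between both groups using analysis of variance for repeated measures".
- Schedule of the primary outcome (Outcome measurements): VAS is measured "at baseline, 20 days of the treatment duration and 1- and 3-month follow-up".
- Expected loss (Sample size considerations): "Considering 20 % loss to follow-up, the total sample size needed to detect this difference at a 5 % level of significance" and a stated power of 90% is 240 patients.

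**The concern.** The two statements set membership of the analysis by different events. Intention-to-treat sets it by randomisation; the caption sets it by attendance at a follow-up. The caption's wording would do no work if every randomised patient entered the analysis at every time point.

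The named method adds a third possibility. Classical repeated-measures ANOVA needs a full set of values for each patient, here four (baseline, 20 days, 1 month, 3 months), and usually discards a patient who lacks one. That is how the method usually behaves, not something the article states. The text therefore leaves open three sets: all randomised, available at each visit, and complete at all visits.

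This matters because patients can tell hands-on manipulation from bag traction, and they mark the VAS themselves. Loss that depends on both pain and arm is plausible, though nothing in the article shows it. If it occurs, a comparison of those who returned is no longer protected by randomisation, and it could be reported under the intention-to-treat name.

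**Working it through.** **Inputs from Sample size considerations.** One-sided superiority test with equal groups, alpha 0.05, beta 0.1, about 98 per group, 20% loss, 240 in total. The SD s and the difference δ appear only as symbols.

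**1. The plan's own total.**
- Dividing by the retained share: 98/(1 − 0.20) = 122.5, so 123 per arm and 246 in total (245 if 196 is inflated as one number).
- Multiplying instead: 98 × 1.2 = 117.6, so 118 per arm and 236 in total.
- The stated 240 lies within 3% of each, so it is reproduced. The 98 itself cannot be rebuilt, because s and δ have no values.

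**2. The effect that 98 per group implies.** Solve 2[(z_alpha + z_beta)s/δ]² = 98 for δ/s.
- One-sided 0.05: δ/s = √(2 × (1.645 + 1.282)²/98) = 0.418.
- Two-sided 0.05, for comparison: δ/s = √(2 × (1.960 + 1.282)²/98) = 0.463.

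**3. Patients outside the analysis if the whole allowance is lost at one visit.**
- 0.20 × 240 = 48 outside; 240 − 48 = 192 remain, or 96 per arm.

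**4. Effect on power.** Power = Φ(0.418 × √(n/2) − 1.645), using the unrounded 0.41806.
- n = 98: 90.0%.
- n = 96: Φ(2.896 − 1.645) = 89.5%.

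The allowance does its job on power, so what is left is bias.

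**5. Possible bias (illustration by assumption).** In each arm let p be the share missing and g the mean outcome of missing minus observed patients. The mean over all randomised patients is the observed mean plus p × g. The observed treatment difference is therefore off, in absolute size, by p₁g₁ − p₂g₂. With p = 0.20 in both arms this is 0.20 × (g₁ − g₂).

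| Between-arm difference in gap (SD) | Shift in effect (SD) | Share of 0.418 SD | Share of 0.463 SD |
|---|---|---|---|
| 0 | 0 | 0% | 0% |
| 0.25 | 0.05 | 12% | 11% |
| 0.5 | 0.10 | 24% | 22% |
| 1.0 | 0.20 | 48% | 43% |

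The first row matters as much as the others: if dropouts are worse than those who stay by the same amount in both arms, and loss is equal, the bias cancels. The article gives no information on which row applies.

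**The case against.** A good deal can be said for the article.

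- **The caption does not say that only completers are analysed.** It says that those who completed were included. A reader might infer a stated exclusion rule; the text does not contain one. This stands: exclusion is the natural reading, not a quotation.
- **The caption does not describe a completer analysis.** A patient seen at 20 days and lost later would still be in the 20-day analysis. This stands, and *observed-case* is the right term. Patients with data may also still be analysed in their assigned arm whatever their adherence, which many would call intention-to-treat. Mislabelling is thus a risk and not a declared plan.
- **Listwise deletion is not stated.** It would itself conflict with the caption, since a patient with one completed follow-up would vanish. The article names a family of methods and a software package; the missing-data rule may sit in a full protocol or SAP that is not shown, and its absence is no finding. This stands. The method only adds to the uncertainty about the set.
- **The caption is weak evidence of intent.** It is a past-tense legend although the Trial status section says recruitment was continuing, and the text introducing the figure mentions 6 months while the outcome schedule ends at 3. That lowers its weight but does not remove the conflict.
- **A mixed model on observed values is compatible with the caption and does not by itself remove the bias.** This is correct where observed VAS does not explain the loss, and it is why a sensitivity analysis is part of the fix.
- **The magnitude is assumed.** Also correct: 20% is a sample-size allowance, not a forecast for each visit, and the gaps have no source in the article.

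**Conclusion.** The concern holds as an unresolved conflict over the analysis set of the primary outcome. The article states intention-to-treat in one place and, in another, an inclusion rule that most naturally means observed cases at each visit. The named ANOVA could shrink the set further if applied in its classical form.

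The firm part is the contradiction in the text. The count of 48 of 240 is conditional on the full allowance being lost at the visit analysed. Loss of power is negligible. The bias range in the table rests on equal 20% loss per arm, an assumed between-arm difference in gap, and an effect back-solved from 98 per group.

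A reader might go further and conclude that the trial plans a completer analysis under the intention-to-treat label, or that a bias of a particular size is to be expected. The documents support neither: they do not state such a rule, and they give no data on who would be lost or why.

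**What to change.** 1. Reconcile the Fig. 1 caption with the Statistical analysis section by stating that all randomised patients are analysed in the arm to which they were assigned. The figure can still report how many were observed at each visit.
2. Replace repeated-measures ANOVA for VAS with a likelihood-based mixed model that uses every observed VAS value. A patient who misses one visit then keeps the others. Because the recruitment section has VAS completed before randomisation, including baseline in the outcome vector would let every randomised patient enter the model.
3. Add a delta-adjusted sensitivity analysis that shifts the missing VAS values by arm and shows how large the shift must be to change the conclusion. The mixed model alone does not protect against loss that observed VAS does not explain.
4. Label any observed-case or completer result as supportive.

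The cost is a change of wording and a small amount of extra analysis work. Sample size and visit schedule are untouched. The change should be made before results by arm are seen.

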### Interventions

Eligible patients will be randomized to one of the two arms: the treatment group and the control group. In the treatment group, patients will receive BCT for 20 days, while patients in the control group will receive traction therapy (TT) for 20 days. This study will be administrated at four hospitals. Patients will visit the physician at 1- and 3-month follow-up.

### Treatment group

In the treatment group, patients are requested to be in the sitting position and receive the following treatments: (1) balancing tendon-regulation: a to-and-fro kneading motion is applied three times to relax the muscles in the nuchal midline: splenius capitis, splenius cervicis and the trailing edge of sternocleidomastoid, respectively. Then manipulations of plucking and relaxing the tendons are applied five to seven times over the same area with a force that the patients can tolerate. Finally, rolling the region along the upper back of bladder meidian for five to seven times, (2) balancing osteopathy: firstly, with the patient adopting an upright sitting position, the practitioner holds the patient’s occiput and jaw between his hands and pulls upward forcefully for 9 s and then relaxes for 3 s. While stretching the neck, the physician turns the patient’s head to the front, back, left and right at an angle of roughly 45° three times and then obliquely wrenches the neck at the position that corresponds with the pathological features of the clinical examination and X-rays; if the lesion sites are at C1 to C3, or C4 to C6, or C7 to T1 within the cervical spine unit, the neck will be flexed at 15°, 0°, or 30 to 45°, respectively. The patient then repeatedly rotates their neck to left or right side to roughly 40° degrees on its own at the stretching state of cervical vertebra, and then rotates toward the affected side to the limit of the angle as well as bending the neck forward while the physician gives a vertical pulling and extending force to the patient’s neck. One or more snapping sounds will be heard if the procedure has been successful, (3) balance collaterals-dredging: first, holding the participant’s upper limb and then quickly shaking that upper limb up and down forcefully with a low-amplitude jittery motion, repeated three times. Next, for the ear-lifting method, kneading-pressing and pulling with the thumb and forefinger are then applied to the region of the upper, middle and lower three parts of the helix, respectively, for 30 s with a force that the patient can tolerate. Lastly, pressing with the thumb is repeatedly applied five to seven times along the DU meridian with focus on the acupoints DU4 (*Mingmen*), DU14 (*Dazhui*), DU17 (*Naohu*) and DU20 (*Baihui*).

The patients will received BCT once every other day for 20 min each session and five treatments constitute a course. The patients will be given two courses (a total of 10 times in 20 days) and will visit the physician at 1- and 3-month follow-up.

### Control group

In the control group, patients will received TT. The patient is sitting comfortably and wearing a cloth bag for occipital-jaw traction, with their head bending forwards at an angle of about 10–15°. The traction weight for cervical spondylosis starts at 3 kg and gradually increases to the maximum weight of 6 kg in increments of 0.5 kg each time. The treatment is performed 30 min at a time every other day for a total of 10 times in 20 days.

### Outcome measurements

The primary outcome is pain severity measured with a Visual Analog Scale (VAS) at baseline, 20 days of the treatment duration and 1- and 3-month follow-up. Secondary outcomes include cervical curvature measured using the Borden method, a composite of functional status measured by the Neck Disability Index (NDI), patient health status (evaluated by the SF-36 health survey) and adverse events (AEs) as reported in the trial.

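### The primary VAS analysis spans three post-baseline visits with no deciding visit or model term, so both the type I error and the 90% power depend on how the plan is read

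*Protocol article*

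**What the plan says.** Outcome measurements defines the primary outcome as pain severity on the "Visual Analog Scale (VAS) at baseline, 20 days of the treatment duration and 1- and 3-month follow-up". That is baseline plus three post-baseline visits, none ranked above the others. Assessment of pain repeats the same four times.

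Statistical analysis gives VAS its own method: "The primary outcome, VAS, will be compared between both groups using analysis of variance for repeated measures". It does not say whether the group main effect or the group-by-time interaction decides, or whether baseline is one of the repeated measures. It adds a conditional branch: "If adjustment for possible baseline incomparability is needed, analysis of covariance will be done". The next paragraph, on data in general, says that measurement data are summarised as mean and standard deviation "and analyzed using a *t* test; rates were compared using the chi-square test". The threshold for all of this is a P value below "0.05 will be used to indicated that the difference was statistically significant".

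Sample size considerations opens with "We calculated the sample size for this two-arm trial on the basis of comparing BCT versus TT". It applies a formula for one difference between two means, one-sided, with alpha 0.05 and beta 0.1. This gives about 98 per group, or 240 in total after 20% loss. No value is given for the SD or for delta, and no visit is named.

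**The concern.** A primary hypothesis needs one deciding comparison. Here the endpoint has three post-baseline visits, the model has two terms that involve group, and the sample size belongs to none of them. Two analysts could each follow the text and reach opposite conclusions on superiority, one from the group main effect and the other from the interaction.

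Two properties of the trial depend on the missing choice. If more than one result may carry the claim, the 5% error rate is lost. If exactly one may, its power need not be the stated 90%, because that figure is for a single two-mean difference while the ANOVA group term is an average over visits.

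**Working it through.** **Inputs from the protocol article.** 98 per group after loss, one-sided alpha 0.05, power 90% (Sample size considerations); four VAS times (Outcome measurements).

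**Assumptions, not in the document.** Equal SD at all four visits and one common correlation ρ between visits, taken as 0.5, 0.7 and 0.8.

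**1. The plan's own figure.** With n = 2[(z_α + z_β)s/δ]² and neither s nor δ given, 98 cannot be reproduced forwards. Solved backwards, δ/s = (1.645 + 1.282) × √(2/98) = 0.418. On inflation, 98/0.8 gives 123 per group (about 245 in total) and 98 × 1.2 gives 118 (236 in total). The stated 240 lies between them. With 240 randomised and 20% lost, 96 per group remain, and one-sided power is 89.5%. The figure is coherent for one two-mean contrast.

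**2. False-positive rate by reading.** Simulation with no true effect, 98 per arm, two-sided 5% tests, baseline as one of the four ANOVA visits:

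| What may carry the claim | ρ = 0.5 | ρ = 0.7 | ρ = 0.8 |
|---|---|---|---|
| Group main effect only | 5% | 5% | 5% |
| Group or group-by-time | about 10% | about 10% | about 10% |
| Any of three visit t tests | 12.5% | 11% | 10% |
| Any of these five tests | 16% | 15% | 14% |

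If baseline is left out of the ANOVA, or is less correlated with later visits than they are with each other, the last row runs from about 13% to 16%.

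**3. Power by reading, effect of 0.418 SD at all three later visits.** For a mean over k visits, the SD is √[(1 + (k − 1)ρ)/k], and z = effect/SD × √(98/2) = effect/SD × 7. Two-sided power is Φ(z − 1.96).

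- One visit: z = 0.418 × 7 = 2.926. Power is 83% two-sided and 90% one-sided.
- Group main effect over four visits including baseline: randomisation makes the expected baseline difference zero, so the mean effect is 0.75 × 0.418 = 0.3135.
  - ρ = 0.5: SD 0.791, z = 2.78, power 79%
  - ρ = 0.7: SD 0.880, z = 2.49, power 70%
  - ρ = 0.8: SD 0.922, z = 2.38, power 66%
- Mean of the three post-baseline visits only:
  - ρ = 0.5: SD 0.816, z = 3.58, power 95%
  - ρ = 0.7: SD 0.894, z = 3.27, power 91%
  - ρ = 0.8: SD 0.931, z = 3.14, power 88%

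**4. Is the shortfall only a matter of one-sided against two-sided testing?** No. With 1.645 in place of 1.96, the four-visit main effect has 87%, 80% and 77% power, still below the 90% that a single visit has on the same footing.

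**5. Sensitivity to the equal-SD assumption.** Entry is limited to VAS above 4 and below 8, which may narrow the baseline SD. If it were half the later SD, the variance of the four-visit mean would be [0.25 + 3(1 + 2ρ) + 3ρ]/16. Power would then be 88%, 81% and 78% two-sided. The loss shrinks, but power stays below the 95%, 91% and 88% of the post-baseline mean.

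**The case against.** The strongest reply is that the plan does assign VAS one method. On the ordinary rule that the specific governs the general, the t-test sentence covers the other continuous data, such as the Borden measure, NDI and SF-36. If the group main effect is then taken as the test, the error rate is 5%. This stands in part. No sentence says that VAS is t-tested at each visit, or that any one significant result counts as success. A reader might infer that the trial simply has a 10–16% false-positive rate. The document does not support that as an unconditional statement.

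The multi-test rates also count rejections in either direction. For three visit-wise two-sided tests, the chance of a false result in favour of BCT is 6.3%, 5.5% and 4.9% at ρ = 0.5, 0.7 and 0.8. With one-sided 5% tests, matching the sample-size section, it would be 11.9%, 10.3% and 9.2%.

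A reader might also infer that averaging over visits is bound to cost power because the effect fades once treatment ends at 20 days. No passage supports a fading pattern. With a sustained effect, a post-baseline average has more power than a single visit.

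Finally, the choice of model term is often left to an analysis plan, and none is shown. But the deciding time point is part of the endpoint definition and of the sample-size basis. The article sets out both and leaves them unconnected. Even without the t-test sentence, two ANOVA terms remain with no choice between them.

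**Conclusion.** The concern holds in a conditional form. The primary outcome covers three post-baseline visits, no visit or ANOVA term decides, and the 90% power is tied to no named comparison. The error rate is 5%, about 10%, or up to about 13–16%, according to which results may carry the claim. The reading that keeps 5% does not deliver the stated power if baseline is an ANOVA level: about 66–79% two-sided at 0.418 SD, against about 88–95% for a post-baseline average.

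These ranges rest on assumed correlations of 0.5–0.8 and equal SDs across visits. The 0.418 SD is back-calculated from 98 per group, not stated. The ambiguity itself rests on no assumption and concerns the primary claim, so it should be settled before any outcome data are examined.

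**What to change.** Amend Outcome measurements, Sample size considerations and Statistical analysis together:

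- Name one primary contrast from the repeated-measures model, for example BCT minus TT in VAS at 20 days, the end of treatment. Adjust for baseline VAS in every case, not only if the groups look different, and do not count baseline as an outcome visit.
- Test 1 month and then 3 months in fixed sequence, each only if the preceding test is significant.
- State that the overall group test, the group-by-time test and any visit-wise t test on VAS carry no primary claim.
- State the sidedness of the test, and give delta, the SD and the power for the named contrast.

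Declaring a post-baseline average to be the single deciding contrast would also hold the error rate at 5%. What matters is that one contrast is named.

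No extra patients are needed. At 98 per arm, the day-20 contrast has 83% two-sided power unadjusted. With a baseline correlation r, z = 2.926/√(1 − r²), so power is 87% at r = 0.3 and 92% at r = 0.5 (r assumed). Trial status says recruitment was continuing at submission, so a short amendment before data are seen was feasible. The price is that a benefit appearing only at 1 or 3 months could not be the primary result.
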